## **Secondary outcomes**

The following secondary outcomes will be collected from practices participating in the implementation:

1. Proportion of women having an HPV self-test
2. Proportion of women having either an HPV self-test, clinician HPV test or cervical cytology (uptake of screening)
3. Proportion of women having an HPV test with a positive result for HPV 16, 18 and or HPV 'other'.
4. Proportion of women having an HPV test with a positive result for HPV 'other' who then have a cervical cytology test (as proposed by national screening programme)
5. Proportion of women having an HPV test with a positive result for HPV 'other' and a negative/mild dysplasia cytology result who return for an HPV test after 1 year (as proposed by national screening programme)
6. Proportion of women with HPV 16, 18 attending colposcopy as per triage
7. Prevalence of high-grade lesions (CIN2, CIN3, Carcinoma) among women attending colposcopy

These outcomes will be stratified by, or adjusted for, ethnicity, deprivation index and screening history to understand screening uptake and post-screening care pathways in these groups.

#### **Qualitative outcomes**

8. Barriers and facilitators to the triage system for women with an HPV positive test.
9. Barriers and facilitators to delivering HPV self-testing in primary care.
10. Barriers and facilitators to women beginning screening at 25 years of age.
11. Barriers and facilitators to accessing screening, for women who are not enrolled in primary care.

These outcomes will help inform implementation of the preferred triage system for HPV positive self-tests, and also illuminate any barriers to applying this triage system, supporting an equitable triage system for positive HPV results.

#### **Ethics**

National ethical approval has been granted by the Southern B Health and Disability Ethics Committee (reference number 21/STH/188) with locality assessment approval by Northland DHB, Kaunihera Kaumātua and Te Poutokomanawa.

#### **Steering group**

In accordance with the principles under Te Tiriti o Waitangi the steering group is to work in partnership with the research partners supporting the implementation and delivery of the Te Ara Waiora Trial by providing subject matter and regional expert knowledge and following decision making processes.

Our steering group is chaired by wāhine Māori who live in Te Tai Tokerau. Membership includes:

- Research Kaumātua
- Whānau and Consumer Representative
- Mahitahi Hauora PHE Representative(s)
- Principal Investigator
- Research Project Manager
- Northland District Health Board (NDHB) Colposcopy Representatives
- Equity Lead
- Primary Screening Representative

The steering group will connect the research to communities and mitigate risk. The group will define the mode and frequency of their meetings and at present are meeting monthly.

### **Internal data management committee (DMC)**

We have asked the HRC if an external data monitoring committee is required. In addition we have formed an internal data management committee. to assess data and clinical safety. The DMC will be responsible for monitoring the overall conduct of the clinical trial. Membership of the DMC includes:

- Principal investigator (general practitioner)
- Two lead investigators (gynecologists),
- Study manager
- Study statisticians
- Representatives from Mahitahi Hauora.

The DMC is chaired by an independent researcher (public health physician).

The DMC will provide recommendations about the stopping or continuing of the trial. To contribute to enhancing the integrity of the trial, the DMC may also formulate recommendations relating to the selection/recruitment/retention of participants, their management, improving implementation of the study protocol and retention of participants, and procedures for data management and quality control.

The DMC will be advisory to the steering committee. The steering committee will be responsible for promptly reviewing the DMC recommendations, to decide whether to continue or stop the trial, and to determine whether amendments to the protocol or changes to the study conduct are required.

The group will meet monthly by teleconference during the course of the study to review any issues. The research team based in the community and primary care will have immediate access by phone to one of the group members to discuss any issues as they arise. The group will report to the whole research team as necessary.

### **The partnership: Mahitahi Hauora and Te Tātai Hauora o Hine Victoria University of Wellington**

This project is a partnership between Te Tātai Hauora o Hine Victoria University of Wellington and Mahitahi Hauora. Mahitahi Hauora is Northland's Primary Health Entity (PHE) and is a collaborative endeavour with support from the Northland District Health Board, Māori led health providers, general practice, and Northland Iwi Leaders. Their goal is to support a primary healthcare system that sustains equitable, self-determined wellbeing and ensures every person has an opportunity to live a long and healthy life. In their support letter for the HRC grant application Mahitahi stated:

*"Cervical cancer is a very important issue for both Māori and non-Māori in Te Tai Tokerau. Any proposed new screening programme should be acceptable and effective for our population. If we get it right here it will likely be generalisable to the rest of Aotearoa and improve access for Māori with a more effective test to reduce cervical cancer disparities."*

Mahitahi are involved at all levels, contribute and co-fund research staff, have membership on the steering committee and internal monitoring group and we will work closely with them. The Hauora will have ownership of their data and all results and publications will be approved by them. This partnership is much valued and there will many opportunities for learning from each other. The project includes local workforce development as there are named investigators from Mahitahi and they will be involved in all research outcomes as well as governance and advisory roles. Consultation for this study has occurred with GPs, PHE, community and DHB in Te Tai Tokerau region.

### **Study Population: Māori and non-Māori women aged 25-69 years living in Te Tai Tokerau/Northland region**

Our study site is Te Tai Tokerau where Māori women have almost twice the incidence of cervical cancer compared to non-Māori and almost four times the mortality. In Northland, cervical screening coverage for Māori is approximately 66% (Table 1).

**Table 1: NCSP coverage (%) in the three years ending 31 March 2016 by ethnicity, women aged 25–69 years, Northland District Health Board**

| Ethnicity      | Population    | Women screened in last 3 years | 3-year coverage | Additional screens to reach 80% target* |
|----------------|---------------|--------------------------------|-----------------|-----------------------------------------|
| Māori          | 12,680        | 8,398                          | 66.2%           | 1,746                                   |
| Pacific        | 691           | 408                            | 59.0%           | 145                                     |
| Asian          | 1,692         | 1,004                          | 59.3%           | 350                                     |
| European/Other | 26,874        | 21,208                         | 78.9%           | 291                                     |
| Total   | 41,937 | 31,018                  | 74.0%    | 2,532                            |

*\*For the total population the number of additional screens is the number required to move from the total population coverage to 80%. This may not be the same as the sum of additional screens required for each ethnic group to reach 80%.*

### Inclusion criteria

The NCSP eligibility policy is that “anyone with a cervix or vagina who has ever been sexually active should be offered three-yearly cervical screening from age 25 to age 69.” For this study all women aged 25.00 to 69.99 years and eligible for cervical screening to prevent cervical cancer in the year of the implementation. Includes first cervical screening test (HPV self-taken or clinician taken swab test, or cervical smear for cytology) for women aged 24.5 years and women who have a routine cervical screening test (HPV self-taken or clinician taken swab test) for cytology up to 6 months BEFORE their cervical screening test due date.

Women who have symptoms raising the possibility of cervical cancer, including post-coital bleeding, unexplained intermenstrual bleeding, any post-menopausal bleeding, unexplained persistent unusual vaginal discharge or unexplained persistent deep dyspareunia should have an HPV test but the focus for these women is primary care follow-up investigation of their symptoms.

### Exclusion criteria

Women who have had treatment for cervical abnormalities and are under active follow up (e.g. still undergoing test of cure) are not eligible. A test of cure is HPV testing and cytology (co-testing) on two occasions, 12 months apart. Women who have had treatment for cervical abnormalities in the past and are overdue for test of cure are eligible.

### Sample size

The NSCP coverage report from December 2019 for the Northland DHB shows that approximately 72.5% of women (33,403/46,090) aged 25-69 were screened over a period of 3 years. A total of fourteen practices and 5600 women (seven practices offering HPV-self-testing universally over a one-year period to approximately 2800 women, and seven practices providing routine clinical care

 HDEC amendment approved December 2021

data for approximately 2800 women about cervical cytology uptake) will give 95% power at a one-sided significance level of 2.5% to detect a non-inferiority margin of 10% between the two groups (i.e. the screening rates at participating practices will be no worse than 10% less than the screening rate obtained from the comparative data). This margin of error was chosen as we believe it is the smallest value that is clinically relevant. For this sample size we assumed a screening rate of 72.5% in the comparative data and 72.5% in the participating practices, and an average practice size of 400 participants and intra-cluster correlation coefficient of 0.01.

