#### *Universal offer of HPV self-testing*

The *universal offer of HPV self-testing* approach means all eligible wāhine will be offered an HPV self-test as the primary screening test. If the wāhine declines the self-test, she will be offered the conventional cervical cytology screen.

We do not yet know the best models for implementation of a high quality effective HPV testing program utilising universal offer of HPV self-testing approach for all eligible women.

Before adopting *universal offer of HPV self-testing* as the primary approach for the NCSP it must be proven that it achieves coverage results that are non-inferior (at least equal) to the present programme. Screening coverage is the proportion of eligible women screened in the previous three years. A screen is defined as either an HPV self-test, clinician taken HPV test or cervical cytology. The MOH target is to reach 80 percent screening coverage for all eligible women, including separately for women in Māori, Pacific, Asian and European/Other population groups.

In addition, triage and referral to colposcopy after a positive high risk HPV test needs to be trialled to ensure these pathways are equitable.

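### The planning rate of 72.5% is three-year coverage of all women, but the comparison covers 12 months in women due a screen, so the endpoint, the base rate and the -10 limit do not refer to the same quantity

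*Protocol*

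**What the plan says.** The Sample size section takes its rate from a coverage report that "shows that approximately 72.5% of women (33,403/46,090) aged 25-69 were screened over a period of 3 years". The same paragraph then uses it for both arms: "For this sample size we assumed a screening rate of 72.5% in the comparative data and 72.5% in the participating practices". The design is described as "A total of fourteen practices and 5600 women (seven practices offering HPV-self-testing universally over a one-year period to approximately 2800 women", with seven comparison practices supplying data on a similar number. The remaining inputs are "an average practice size of 400 participants and intra-cluster correlation coefficient of 0.01". The claim is that this "will give 95% power at a one-sided significance level of 2.5% to detect a non-inferiority margin of 10% between the two groups". The margin is justified only by the investigators' belief that it is the smallest clinically relevant value.

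The period and population of the comparison appear elsewhere:

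- **Aim:** the hypothesis concerns women due a screen, including those under-screened and never screened.
- **Inclusion criteria:** women must be "eligible for cervical screening to prevent cervical cancer in the year of the implementation". A first test at age 24.5 and a routine test up to six months before the due date also count.
- **Stage Two:** the non-inferiority question is to be answered in 12 months.

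The outcome is named differently in different places. Data analysis compares screening coverage against a limit of -10. The section on the universal offer says "Screening coverage is the proportion of eligible women screened in the previous three years". Study design speaks of uptake, and Secondary outcomes lists uptake of screening separately.

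**The concern.** A woman screened in the two years before the trial counts towards 72.5% coverage, but she is generally not due in the trial year. Coverage of the whole age group over three years and uptake over one year among women due are therefore different proportions, with different numerators and denominators. Using the first to plan a comparison of the second gives the wrong binomial variance. It also leaves open what the 10 points are 10 points of.

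The margin decides the trial's conclusion, and the protocol says non-inferiority must be shown before the approach becomes the national one. A reader of the result needs to know which loss of screening was ruled out. This goes beyond detail that a statistical analysis plan could supply, because the protocol has already fixed a definition, a rate, a margin and a power that do not fit together.

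**Working it through.** **Inputs (Protocol, Sample size).** 33,403/46,090 = 72.5% in both arms; margin 0.10; one-sided 2.5%; 7 practices of 400 women (2800) per arm; ICC 0.01.

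**1. The plan's own figure.**
- Design effect = 1 + (400 - 1) x 0.01 = 4.99. Effective n per arm = 2800/4.99 = 561.
- SE = sqrt(2 x 0.725 x 0.275/561) = 0.0267.
- Normal power = Phi(0.10/0.0267 - 1.96) = 96.3%.
- With a t reference on 12 df (14 practices less 2 arms), power = 93.0%. A pooled two-proportion formula at 72.5% against 62.5% gives 94.8%.
- The stated 95% is reproduced.

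**2. One-year uptake in women due (assumption needed).** The protocol gives no such rate. Assume a steady state: screens spread evenly over the three-year interval, one per woman.
- Screened per year: 72.5/3 = 24.2% of all women.
- Due in a year: 24.2% falling due + 27.5% overdue = 51.7%.
- Uptake = 24.2/51.7 = 46.8%.

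The same formula with other inputs:

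| Input | Uptake |
|---|---|
| Table 1 total coverage, 74.0% | 48.7% |
| Table 1 Māori coverage, 66.2% | 39.5% |
| 72.5%, with women up to 6 months before their due date also in the denominator: 24.2/(1.5 x 24.2 + 27.5) | 37.9% |

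The range is about 38-49%.

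**3. Power with only the rate changed.**

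| Rate in both arms | SE | Normal | 12 df |
|---|---|---|---|
| 72.5% (stated) | 0.0267 | 96.3% | 93.0% |
| 38% | 0.0290 | 93.2% | 88.6% |
| 46.8% | 0.0298 | 91.9% | 86.8% |
| 50% (largest variance) | 0.0299 | 91.8% | 86.7% |

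Because p(1 - p) peaks at 50%, no base rate takes power below the last row while the other inputs stand.

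**4. What 10 points means on each scale.**
- Relative loss: 10/72.5 = 14%; 10/47 = 21%.
- Converted to long-run coverage: uptake u in the steady-state model corresponds to coverage 3u/(1 + 2u). At u = 46.8% this is 72.5%. At u = 36.8% it is 1.104/1.736 = 63.6%. Ten points of uptake is thus about 8.9 points of eventual coverage.
- Three-year coverage of all women, measured after 12 months: two of the three years precede the trial and are cytology in both arms. A 10-point fall must come entirely from the trial year, so annual screens go from 24.2% to 14.2% of women, and 10/24.2 = 41% of the year's screens are lost.

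**The case against.** The strongest reply is that nothing has been miscalculated and that the consequence for power is small. Both parts stand. The 95% follows from its inputs, and on the normal basis that best matches it, changing the rate alone gives about 92%. The step from 92% to 87% comes from the 12-df reference, which also lowers the stated inputs to 93.0% and is a choice an analysis plan may make. A reader might infer that the trial is seriously underpowered; the figures do not support that.

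A reader might also take 47% as implied by the protocol's own numbers. It is not. It needs the steady-state assumption, and the protocol itself reports a sharp fall in screening since COVID-19. Stage One practices are also drawn from those with at least 15% Māori, so a DHB-wide rate need not apply to them.

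Nor is the margin shown to be extreme. On the due-in-year reading, the higher relative loss (21%) is offset by the conversion to about 9 points of long-run coverage. The 41% figure belongs to the other reading of the endpoint, and the two cannot both apply.

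Finally, the three-year definition stands in the Overview beside the national target and may describe the national indicator, not the trial endpoint. That is a fair reading, and the one-year outcome in women due is the better supported. But Data analysis uses the same term, and no section says that it means something else there.

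**Conclusion.** The mismatch is real and stands on the protocol's text alone: a three-year rate for all women aged 25-69 is used for a 12-month comparison in women due, with an outcome whose name carries a three-year definition. Neither reading of the endpoint makes the parts agree. If the endpoint is one-year uptake in women due, 72.5% is the wrong base rate and the margin was not justified against the right one. If it is three-year coverage of all women, the result is diluted by pre-trial screens and the test is too lenient.

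The effect on power is modest: about 92-93% (normal) or 87-89% (12 df) in place of the stated 95%, over assumed rates of 38-49% and with the ICC and practice sizes as stated. The effect on the margin matters more. It is unanchored, though not shown to be extreme. The 47% and the margin conversions rest on the steady-state assumption; the inconsistency does not.

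**What to change.** - **Outcome.** State the primary outcome once, as a screen within the 12-month window among women due or overdue at its start or falling due during it. Make the denominator agree with Inclusion criteria, including women aged 24.5 and those screened up to six months early. Use one term for it throughout and keep the three-year definition for the national indicator.
- **Base rate.** Replace 72.5% with the rate on that same definition for a pre-trial year. The NSU, already named as the source of screening history, is the natural place to obtain it.
- **Margin.** Justify the 10 points against that rate, giving the relative loss it allows.
- **Power.** Restate power for 5600 women in 14 practices over a range of rates. At 47% it is about 92% (normal) or 87% (12 df).

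The cost is protocol wording and one recalculation, and a slightly less favourable stated power. No extra women or practices are needed if that power is accepted. It should be done before the data are analysed, because it settles what the decision threshold means.

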### **Practice selection**

In total there are 28 practices from Mahitahi that are eligible (women aged 25-69 and practice is able to provide data). Of these there are 22 practices that have a moderate to high proportion of Māori ( $\geq 15\%$  of the practices population).

To inform the implementation of the new NCSP, at the direct request of the NSU, the original HRC funded study will be broadened to include more practices and address the study aims in a shorter time. As the original study is already underway, a two-stage process of practice randomisation and selection is required.

### **Stage One**

Four practices will be randomly selected from the 22 eligible practices that have a moderate to high proportion of Māori, and this random selection will be stratified by practice size and rurality. To do this the 22 practices will be divided into the following four population size by rurality groups: small-rural, small-urban, large-rural and large-urban. Within each of the population size by rurality groups, one practice will then be randomly selected using computer generated random numbers (which gives a total of four practices). The randomisation sequence will be generated by the trial statistician.

Consent to participate in the implementation will be sought from each of the four practices. If a practice does not consent, then another practice will be randomly selected that has the same population size by rurality group.

### **Implementation practices:**

The four practices will provide a *universal offer of an HPV self-test* approach. Practice staff will be encouraged to invite the women to self-test. Posters and flyers with self-test HPV information will be displayed in these practices. HPV swabs and self-tests are funded by the study and there will be no charge for women. However normal service fees for the practice will apply. For example, if an eligible woman comes into the practice for a consult and is opportunistically screened she will be charged for the consultation as usual but there will be no additional charge for the HPV test.

### **Comparison practices:**

Four practices (but with similar characteristics to the implementation practices) will be asked retrospectively for permission to access data from records obtained through clinical care for comparison to the implementation practices. De-identified data for the same period as the implementation trial will be requested retrospectively. If a practice does not give permission to access data, another practice will be approached until four practices have given permission.

Any changes over time in this usual standard care for each practice will be documented.

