#### **Comparison practices**

Seven similar Mahitahi primary care practices (the comparative practices) who will be business as usual offering cervical cytology screens will be asked for permission to retrospectively access their screening data. De-identified data for the same period as the implementation trial will be requested.

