### **Stage Two**

To enable availability of research findings in a timely manner to inform the national screening programme the number of practices was increased to 14 practices (seven implementation

practices and seven comparison practices). This will achieve the primary aim of testing the “non-inferiority hypothesis” in 12 months. Please see the “Sample size” section for further detail.

The same methods used above in stage 1 will be used to randomly select an additional three practices for the implementation arm from the remaining eligible practices. The random selection will be stratified by practice size and rurality. Within each of the small-rural and small-urban practices, one practice will be randomly selected (n=2). The third practice will be randomly selected from the large practices. This gives a total of seven practices in the implementation arm.

An additional three practices with similar characteristics to the implementation practices will be asked for permission to retrospectively access data from records obtained through clinical care for comparison to the implementation practices.

At the completion of Year 1 the study will have reached the number of participants needed for analysis. In agreement with the Ministry of Health we will offer HPV self-testing in Year 2 to comparison clinics for up to one year or until the new national screening programme starts. Women will still be asked to complete a consent form as this will be part of the research. The research team will use canSCREEN as the database for this group to ensure clinical safety.

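### The protocol states no random or pre-specified rule for choosing comparison practices, so entry to the comparator arm is open to selection related to the outcome

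*Protocol*

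**What the plan says.** For the implementation arm, the Protocol (Stage One) divides the 22 practices with a moderate to high proportion of Māori into four size-by-rurality groups and states: "Within each of the population size by rurality groups, one practice will then be randomly selected using computer generated random numbers". Refusal is covered by the same device: "If a practice does not consent, then another practice will be randomly selected that has the same population size by rurality group". Stage Two applies the same method to three further practices, and names the implementation arm only.

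For the comparison arm, the section on comparison practices under Stage One gives similarity to the implementation practices as the only criterion. These practices "will be asked retrospectively for permission to access data from records obtained through clinical care for comparison to the implementation practices", and "De-identified data for the same period as the implementation trial will be requested retrospectively". Refusers are handled thus: "If a practice does not give permission to access data, another practice will be approached until four practices have given permission". Stage Two adds: "An additional three practices with similar characteristics to the implementation practices will be asked for permission to retrospectively access data". The design section says of all seven that they "will be asked for permission to retrospectively access their screening data".

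The Data analysis section makes the primary outcome a direct comparison of coverage between these two sets of practices. Non-inferiority is declared if the lower 95% limit of the difference lies above -10. Adjustment for age, ethnicity, deprivation, screening history and practice is planned as a sensitivity analysis.

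**The concern.** The protocol sets a selection procedure for both arms, but only one arm gets a rule that could be reproduced. For the comparators it does not say who selects, from which list, in what order, or within which groups, and the Stage One wording places the request for permission after the outcome period. A practice can therefore enter or drop out for reasons linked to its screening coverage, which is the primary outcome.

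The direction is not determined. If practices with high coverage are missed or decline, the comparator rate falls and non-inferiority is easier to declare wrongly. If practices with low coverage decline, the comparator rate rises and a truly non-inferior programme may fail. The result is meant to inform a national programme, so either error matters.

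**Working it through.** **Inputs** (Protocol, Sample size and Practice selection): 7 practices per arm, 400 women per practice, 2800 women per arm, intra-cluster correlation 0.01, coverage 72.5% in both arms, margin 10 points, one-sided 2.5%, stated power 95%. There are 28 eligible practices, of which 22 have at least 15% Māori.

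**The plan's own figure.**
- Design effect = 1 + (400 - 1) × 0.01 = 4.99.
- Effective n per arm = 2800 / 4.99 = 561.
- Standard error of the difference = √(2 × 0.725 × 0.275 / 561) = 0.0267.
- Power = Φ(0.10 / 0.0267 - 1.96) = 96.3%. With a t reference on 12 degrees of freedom it is 93.0%.
- Required n: 519 per arm × 4.99 = 2590, or 6.5 practices, rounded up to 7.

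The stated 95% is reproduced to within rounding and choice of reference distribution. It presumes that the comparators are a fair sample.

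**Room for selection.** After seven implementation practices are taken, 22 - 7 = 15 candidates remain (28 - 7 = 21 if the wider list is used) for seven places.

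**Spread between practices.** √(0.01 × 0.725 × 0.275) = 0.0447, about 4.5 points.

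**Shift in the comparator mean.** Both scenarios are assumptions.
- Mild: 20% of practices refuse, with a correlation of 0.3 between coverage and refusal. The mean of a standard normal variable cut at its 80th percentile is displaced by 0.35, so the shift is 0.3 × 0.35 × 4.47 = 0.47, about 0.5 points.
- Strong: all permission-givers come from one half of the distribution. The half-normal mean is 0.798, so the shift is 0.798 × 4.47 = 3.6 points.

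**Effect on the decision rule.** Take a true difference of -10 points and a comparator biased downwards, with the standard error held at 0.0267. The one-sided error is Φ(-1.96 + shift / 0.0267).
- Mild: Φ(-1.96 + 0.18) = about 0.04.
- Strong: Φ(-1.96 + 1.34) = about 0.27.

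**Simulation.** This used 100,000 runs with the same inputs. The practices that drop out are assumed to be those with the highest, or the lowest, observed coverage among those approached. Paired values are for a normal and a t analysis.

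| Assumed drop-out | Comparator shift (points) | One-sided type I error at -10 | Power at zero difference |
|---|---|---|---|
| None (random draw) | 0.0 | 0.026 / 0.025 | 0.963 / 0.929 |
| Highest 1 | -1.0 | 0.055 / 0.062 | 0.987 / 0.978 |
| Highest 2 | -1.7 | 0.088 / 0.106 | 0.994 / 0.991 |
| Highest 3 | -2.3 | 0.124 / 0.155 | 0.997 / 0.996 |
| Lowest 1 | +1.0 | 0.008 / 0.013 | 0.925 / 0.902 |
| Lowest 2 | +1.7 | 0.004 / 0.008 | 0.883 / 0.870 |
| Lowest 3 | +2.3 | 0.001 / 0.004 | 0.838 / 0.838 |

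These rows assume that drop-out follows coverage perfectly. They show how sensitive the rule is to a few practices and do not forecast what will happen.

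**The case against.** The strongest reply is that the text shows no actual selection on outcome. Comparators must resemble the implementation practices, which should remove part of the between-practice spread used above. Their outcome data come from the National Screening Unit (Data collection, extraction and management), so practices do not measure their own result. They give only de-identified data and are offered self-testing in Year 2, so refusals may be few. Retrospective access also protects usual care from being changed by observation. All of this is fair, and it argues for the lower end of the range. None of it determines which practices enter the arm.

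The adjusted sensitivity analyses help with measured differences between women. They are secondary and cannot remove selection on unmeasured practice factors. Adjusting for practice cannot help either, because each practice belongs to one arm.

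Stronger readings are tempting but unsupported:
- A reader might infer that comparators are chosen by someone's judgement. The protocol does not say how they are chosen.
- A reader might infer that practices or the primary health entity know their coverage when permission is sought. No passage says so.
- A reader might infer that every approach comes after the outcome period. Only the Stage One text puts the request itself in retrospect. In the design section and Stage Two the word describes access to the data, and the Year 2 offer means the comparison clinics must be identified by about the end of Year 1.
- A reader might carry replacement until the quota is met over to all seven. It is stated only for the four Stage One practices.
- A reader might conclude that the random draw is worthless. It still serves its stated purpose of a representative implementation sample.

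**Conclusion.** The point holds in this form: one arm has a random, stratified selection and replacement rule, the other has none stated, and the comparator is therefore open to outcome-related selection in either direction. The size cannot be known from the documents. Under the protocol's own correlation and coverage, the assumed scenarios give a comparator shift of about 0.5 to 3.6 points, which is 5% to 36% of the 10-point margin. The upper figure needs a 50% refusal governed entirely by coverage, and both figures use the full between-practice spread with no credit for matching. Even so, losing one or two practices at the top of the coverage range would raise the one-sided error from 2.5% to roughly 6% to 11%. This is a weakness in the selection procedure that is cheap to close. It is not evidence that the comparison is biased.

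**What to change.** Before any comparator outcome data are viewed, have the trial statistician draw the seven comparison practices at random from the remaining eligible practices, within the same size-by-rurality groups used for the implementation arm. Record a random order of replacements within each group, and apply it to both stages. State which list (22 or 28 practices) the draw uses. Report every refusal, with the refusing practice's prior coverage where available, beside that of the practices included.

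This extends the protocol's own Stage One rule to the other arm. It costs one further random draw and a short amendment, and the sample size does not change. The number of practices in each group is not given, so a rule is needed for a group that runs out.

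Data access can stay retrospective. Asking permission in advance is optional, and its small downside is that comparators would know their routine data will be used. Randomising the Stage Two practices jointly to the two arms would be a larger change and would not cover the four Stage One implementation practices. With either approach the overall comparison remains non-randomised, and the protocol and reports should say so.
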